#### Secondary Outcomes

For quantitative data (such as NRS-11, SF-12, and PSQI scores), the t-test or Mann–Whitney U test will be used to compare the differences between the two groups according to the data distribution characteristics. For categorical results (such as complication rate), chi-square test or Fisher's exact test will be used. All statistical analyses will use two-sided tests, with the significance level set to 0.05. For continuous repeated measurement data, such as quality of life scores at different time points after treatment, repeated measures ANOVA or mixed models will be used to analyze data for time effects and between-group effects.

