## Background

Herpes zoster (HZ), commonly known as shingles, is a painful dermatological condition triggered by the reactivation of the varicella-zoster virus (VZV). Approximately 30% of individuals are at risk of developing HZ over their lifetime if not vaccinated [1]. This virus resides in a dormant state within the dorsal root or trigeminal ganglia in adults. Its reactivation induces acute neuroinflammation and subsequent long-term damage to neurons and supportive cells, resulting in persistent pain known as zoster-associated pain (ZAP). Postherpetic neuralgia (PHN) is conventionally defined as pain in the affected dermatome that persists for at least 3 months after the healing of the acute herpes zoster rash [2]. Patients over the age of 50 are more likely to develop HZ [3, 4]. PHN can significantly impact patients' quality of life, causing persistent pain that interferes with daily activities and sleep.

Antiviral treatment is the cornerstone of HZ management, aiming to reduce viral replication, accelerate lesion healing, and alleviate acute pain. Common antiviral agents include acyclovir, valacyclovir, and famciclovir, which inhibit viral DNA synthesis. Despite their efficacy in reducing acute pain and viral shedding, antiviral medications have limitations. They do not completely prevent the development of PHN, particularly in patients with severe initial pain, older age, combined with underlying diseases or compromised immune systems [5, 6]. The partial efficacy of antivirals underscores the need for adjunctive therapies to more effectively manage ZAP and prevent its progression to PHN [7]. Studies highlight the thoracic region as the most commonly affected area [8].

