#### Primary Outcome

A chi-square test will be used to compare the incidence of PHN between the PRP treatment group and the antiviral therapy group. Additionally, the relative risk (RR) and its 95% confidence interval will be calculated to evaluate the relative risk of PRP treatment compared to antiviral therapy.

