#### Sample Size Calculation

Based on the reported prevalence, the incidence of PHN after antiviral therapy with famciclovir after VZV relapse in patients > 50 years of age is approximately 34.8%[31]. We predict a similar incidence rate in the control group. For the PRP group, our clinical experience suggests an estimated incidence of 10%. To achieve a 90% confidence level and a 5% significance level, we used PASS V.15 software (NCSS, Kaysville, UT, USA) to estimate that a minimum of 58 patients per group is required. Considering a potential 10% dropout rate, we plan to recruit 64 patients per group, totaling 128 patients.

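### NRS-11, SF-12 and PSQI are compared with no stated baseline covariate and no main method; one baseline-adjusted mixed model per score would gain precision at almost no cost

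*Protocol article*

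**What the plan says.** Protocol article, Statistical Analysis:

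- Primary Outcome: "A chi-square test will be used to compare the incidence of PHN between the PRP treatment group and the antiviral therapy group", with a relative risk and 95% confidence interval. No covariate is named.
- Secondary Outcomes, quantitative scores: "the t-test or Mann–Whitney U test will be used to compare the differences between the two groups according to the data distribution characteristics".
- Secondary Outcomes, repeated scores: "repeated measures ANOVA or mixed models will be used to analyze data for time effects and between-group effects". The example given is quality of life at time points after treatment. An arm-by-visit term is not mentioned.
- Handling of Outliers and Missing Data: missing values are to be multiply imputed.

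Table 1 and the Data Collection and Management section show NRS, SF-12 and PSQI measured before treatment. After that, Table 1 has nine NRS visits (weeks 1–4 and months 1, 2, 3, 6 and 12) and four SF-12 and PSQI visits (week 4 and months 3, 6 and 12). The Background says antivirals fall short of preventing PHN "particularly in patients with severe initial pain, older age, combined with underlying diseases or compromised immune systems". Randomization and Blinding describes blocks of 4 and mentions no stratification.

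**The concern.** A patient's starting score usually predicts the later score on the same scale. A two-sample t-test or Mann–Whitney test has no place for it, and the repeated-measures sentence gives it none. The variation it could explain therefore stays in the error term.

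Four candidate methods cover the same data: t-test, Mann–Whitney, ANOVA and mixed model. The first pair is chosen after looking at the distribution, and that choice changes what is estimated (a difference in means or a comparison of ranks). The two effects named for the repeated analysis, time and overall group, do not give the arm difference at a particular visit. For NRS, an overall group effect averages the four-week injection period with follow-up to 12 months.

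This matters because Study Objectives includes relief of acute pain in the primary objective, while the only primary outcome is PHN from month 3 onwards. The evidence on acute pain therefore rests on the NRS analysis.

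**Working it through.** **1. The plan's own figure.** Inputs from Sample Size Calculation: control incidence 34.8%, PRP incidence 10%, and "To achieve a 90% confidence level and a 5% significance level", where I read the 90% as power. Secondary Outcomes gives the tests as two-sided. With pooled variance under the null and no continuity correction:

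n = [1.960·√(2·0.224·0.776) + 1.282·√(0.348·0.652 + 0.10·0.90)]² / (0.348 − 0.10)²
= (1.156 + 0.721)² / 0.0615 = 57.3, so 58 per group.

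This matches the protocol exactly. The unadjusted chi-square is thus consistent with the sample size, and nothing below alters that figure.

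**2. Gain from adjustment for the continuous scores.** The documents give no correlation r between baseline and follow-up, so r = 0.3 to 0.6 is assumed. Adjustment for baseline multiplies the error variance by 1 − r², which is equivalent to multiplying the sample by 1/(1 − r²). With 58 evaluable patients per arm, the unadjusted difference detectable at 80% power is (1.960 + 0.842)·√(2/58) = 0.52 SD. With adjustment it is 0.52·√(1 − r²).

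| r (assumed) | 1 − r² | Variance removed | Equivalent n per arm | Detectable difference |
|---|---|---|---|---|
| none | 1.00 | 0% | 58 | 0.52 SD |
| 0.3 | 0.91 | 9% | 58/0.91 = 64 | 0.50 SD |
| 0.5 | 0.75 | 25% | 58/0.75 = 77 | 0.45 SD |
| 0.6 | 0.64 | 36% | 58/0.64 = 91 | 0.42 SD |

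The gain in effective sample size is 1/0.91 = 1.10 to 1/0.64 = 1.56, that is 10–56%. Power for a 0.5 SD difference is 76.8% unadjusted, 80.6% at r = 0.3 and 87.5% at r = 0.5.

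**3. If change from baseline was meant.** The protocol does not say whether the score or its change is tested. With equal variances, a change score has variance 2(1 − r) relative to the raw score: 1.4, 1.0 and 0.8 at r = 0.3, 0.5 and 0.6. Each exceeds the adjusted value of 0.91, 0.75 and 0.64, so covariate adjustment is the more precise choice under that reading too.

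**4. Loss of patients under repeated-measures ANOVA.** If ANOVA were run on complete cases, with a share m missed independently at each of k visits, (1 − m)^k of patients would remain. For NRS (k = 9), m = 2% leaves 0.98⁹ = 83% and m = 5% leaves 0.95⁹ = 63%. For SF-12 and PSQI (k = 4) the figures are 92% and 81%. Both m values are assumptions. The planned multiple imputation fills the gaps before any ANOVA, so under the plan as written this loss does not arise.

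**The case against.** Three points can be made for the plan.

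- *The documents do not show that baseline is ignored.* The article is condensed, a statistical analysis plan may list covariates, and nothing rules out a baseline term in the mixed model. This stands, so it would be too strong to say the baseline scores go unused. What can be said is that the stated methods give them no role. A t-test or Mann–Whitney comparison of scores cannot take a covariate, and the repeated-measures example covers scores after treatment only.
- *Visit-level contrasts could come from the two-sample tests.* They could, but without baseline, and without any statement of which of the four methods is the main one.
- *The gain is assumed.* This is true. The entry rule of NRS at least 4 narrows the baseline range and may lower r for pain. SF-12 and PSQI have no such entry restriction.

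A reader might also infer two stronger criticisms. The first is that ANOVA would discard 17–37% of patients and so conflict with intention-to-treat. The documents do not support this: multiple imputation is planned, mixed models are named as an alternative, and no complete-case analysis is proposed. The second is that chance imbalance in initial pain or age biases the PHN comparison. It does not. Under randomisation the chi-square test is valid, and its error rate already allows for such imbalance.

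**Conclusion.** The point holds as a free improvement for the continuous secondary outcomes. The stated analyses are valid but less precise than they could be, and the either/or choices leave the main estimate undetermined. The size is 9–36% of the error variance, or about 10–56% more patients, if baseline and follow-up correlate at 0.3–0.6. That range is an assumption, and pain may lie near its lower end.

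For PHN there is nothing to correct. The chi-square test and relative risk are sound and match the method that gives 58 per group. Adjustment there would improve precision, by an amount not quantified here because the 1 − r² rule applies to continuous scores.

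**What to change.** In Statistical Analysis, Secondary Outcomes, replace both either/or choices with one mixed model per score (NRS-11, SF-12, PSQI). Each model contains baseline score, arm, visit and arm-by-visit. Report the arm difference with its 95% confidence interval at visits named in advance. Delete the repeated-measures ANOVA option and the choice of test by observed distribution. Add a sentence on how the planned multiple imputation fits with this model.

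In Statistical Analysis, Primary Outcome, keep the chi-square test and relative risk. Add a relative risk and risk difference adjusted for baseline NRS and age, for example from modified Poisson or standardised logistic regression, at the same visit or visits as the chi-square. At the planning rates, 58 per arm gives about 0.348·58 + 0.10·58 = 26 PHN cases, so the adjustment should stay with these two covariates.

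The cost is wording and a little more analysis work. Baseline NRS, SF-12 and PSQI and demographic data are already collected, and the sample size does not change.

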## Abstract

**Background:**

Herpes zoster (HZ), triggered by the reactivation of the varicella-zoster virus, manifests as a painful rash known as zoster-associated pain (ZAP), which can progress to postherpetic neuralgia (PHN). This study evaluates the efficacy and safety of ultrasound-guided thoracic paravertebral injections of platelet-rich plasma (PRP) in managing acute ZAP and preventing PHN.

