#### Ultrasound-Guided Thoracic Paravertebral Injection Technique

We adopted an ultrasound-guided approach for thoracic paravertebral injection, as detailed in Pu et al. [25]. The patient will be placed in the prone position to optimize access to the thoracic paravertebral space. A low-frequency convex array ultrasound probe (2–5 MHz) will be used to localize the target thoracic levels, starting in the paraspinal sagittal position and moving caudally to identify the ribs. After identifying the first rib, the probe will be moved further down the thoracic spine to locate the target segments. Typically, one to three thoracic levels will be selected based on the dermatomal distribution of ZAP, with emphasis on the most affected segments (e.g., T3, T4, and T5 for T3–T5 involvement).

Once the target level is identified, the probe will be rotated 90 degrees to achieve an axial view, allowing visualization of the transverse process, inferior articular process (IAP), and parietal pleura (PP). A 22-gauge, 80–100-mm echogenic needle will be inserted in-plane from lateral to medial, aiming for the midpoint between the IAP and PP. Doppler ultrasound will be used to avoid puncturing vascular structures. After confirming the needle placement, 3 ml of PRP will be injected at each targeted level under continuous ultrasound guidance.

Following the injection, patients will be monitored for 30 min to observe any adverse effects. A follow-up ultrasound will be performed to verify the distribution of the injectate and exclude complications such as hematomas or pleural punctures.

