## Conclusions

This study protocol is designed to assess the efficacy and safety of ultrasound-guided PRP therapy in managing ZAP. Should the research hypothesis be validated, PRP could emerge as one of the viable methods for providing pain relief and enhancing the quality of life for patients suffering from ZAP.

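### The only inferential method stated for safety is a between-arm test of the complication rate, which cannot size the risk of an injection that controls never receive

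*Protocol article*

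**What the plan says.** The abstract, the Key Summary Points and the Conclusions all name safety as something the trial evaluates. The Conclusions put it this way: "This study protocol is designed to assess the efficacy and safety of ultrasound-guided PRP therapy in managing ZAP".

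The injection technique section calls for a repeat ultrasound after each injection, in part to "exclude complications such as hematomas or pleural punctures". Only the PRP arm is injected. Both arms receive famciclovir and may receive analgesics.

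On analysis, the Secondary Outcomes paragraph under Statistical Analysis says: "For categorical results (such as complication rate), chi-square test or Fisher's exact test will be used". It adds that "All statistical analyses will use two-sided tests", "with the significance level set to 0.05". It does not say when chi-square and when Fisher applies, and it names no estimate or interval for the complication rate. The Primary Outcome paragraph just before it does give the PHN comparison a relative risk with a 95% confidence interval.

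The Sample Size Calculation concerns PHN only: 34.8% against 10%, 58 per group, 64 recruited per group. Strengths and Limitations refers to adequate power without restricting that claim to PHN.

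**The concern.** The document does not simply leave safety analysis to a later plan. It chooses a method, uses the complication rate as its own example, and the method fits the question poorly in two ways.

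- **Injection-specific events.** Hematoma or pleural puncture from the procedure cannot occur in patients who have no procedure. The control rate is zero by design, so a p-value against it answers no open question. What matters is how large the rate is in the PRP arm.
- **Sample size.** A trial sized for a 24.8-point difference in PHN has little power for harms of a few percent, whichever arm they occur in.

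At stake is the safety statement in the final report. If the p-value is the main statistic shown, a reader may take a non-significant result for reassurance, and the unrestricted remark about adequate power would encourage that.

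**Working it through.** **Inputs from the protocol.** Two-sided 0.05; chi-square or Fisher; 1:1 allocation; 64 recruited and 58 evaluable per arm; PHN 34.8% against 10%.

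**Inputs assumed.** The protocol gives no complication rate. I take 0% in controls for injection-specific events and show a range for the PRP arm, with 64 per arm and no loss.

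**Step 1. The plan's own sample size.** I read "To achieve a 90% confidence level and a 5% significance level" as 90% power at two-sided 0.05. The mean rate is (0.348 + 0.10)/2 = 0.224.

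n = [1.960 × √(2 × 0.224 × 0.776) + 1.282 × √(0.348 × 0.652 + 0.10 × 0.90)]² / 0.248² = (1.156 + 0.721)² / 0.0615 = 57.3, so 58 per group.

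This matches the protocol. It is a calculation for PHN and says nothing about complications.

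**Step 2. Events needed for significance against 0 of 64.**

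- Fisher, two-sided, k against 0: p = 2 × C(64,k)/C(128,k). For k = 5, p = 0.058; for k = 6, p = 0.028. At least 6 events are needed.
- Uncorrected chi-square, k against 0: X² = 128k/(128 − k). For k = 3, X² = 3.07 and p = 0.080; for k = 4, X² = 4.13 and p = 0.042; for k = 5, X² = 5.20 and p = 0.023. Four events are enough.
- With Yates' correction the threshold is 6, as for Fisher.

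**Step 3. Chance of missing a true rate.** With a control rate of zero, power is P(X ≥ 6) for Fisher and P(X ≥ 4) for uncorrected chi-square, where X is binomial(64, rate).

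| True PRP rate (assumed) | Fisher misses | Uncorrected chi-square misses |
|---|---|---|
| 3% | 99% | 87% |
| 5% | 90% | 60% |
| 8% | 59% | 24% |
| 10% | 37% | 11% |

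Fisher reaches 80% power only at about 12%. With 58 per arm and 5% against 0%, Fisher misses 93% and uncorrected chi-square 67%. At 5% the expected number of events is 64 × 0.05 = 3.2, or 1.6 per cell under the null. At such counts Fisher is the usual choice.

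**Step 4. Events possible in both arms.** Full enumeration of the two binomials with 64 per arm: Fisher misses 90% for 10% against 5%, and 73% for 20% against 10%. Uncorrected chi-square misses 81% and 65%.

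**Step 5. What an exact interval would show.** Two-sided 95% Clopper-Pearson limits for the PRP arm. For 0 events the upper limit is 1 − 0.025^(1/64) = 5.6%.

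| Events in 64 | 95% interval |
|---|---|
| 0 | 0% to 5.6% |
| 1 | 0.04% to 8.4% |
| 3 | 1.0% to 13.1% |
| 5 | 2.6% to 17.3% |

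With 58 patients, 0 events gives an upper limit of 6.2%. Under Fisher, 5 against 0 is not significant (p = 0.058), yet the interval runs to 17.3%, above one in six.

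**The case against.** The other side has several sound points.

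- **The protocol sets no rule that non-significance means safety.** A reader might infer that a p-value above 0.05 will be passed off as safety. No section says so: there is no safety margin and no hypothesis of equal safety. This stands, and the risk lies in how a result could be read.
- **The safety aim does not rest on this test alone.** Another tempting reading is that the test is the whole safety evaluation. It is not. Treatment-related adverse events are recorded and analysed (Outcome Assessment, Secondary Outcomes). Causality, severity and outcome are assessed, and a monitoring committee reviews the data (Data Collection and Management). Dropouts are followed for safety (Case Dropout Instructions). Five events against none would be visible in such reporting. This stands too, but none of these provisions says how a complication rate will be estimated.
- **The 90% belongs to Fisher (or Yates) and to assumed rates.** The wording also permits uncorrected chi-square, which misses about 60% and finds 5 against 0 significant. This stands. Either miss rate is still poor for a safety question.
- **The structural zero covers only injection-specific events.** Reactions to famciclovir or analgesics can occur in both arms. A between-arm comparison is meaningful there, though the power is low.
- **Intervals for adverse events are often left to the full protocol or analysis plan.** That would settle the matter if the article were silent. It instead names a test for this very outcome, and that choice can be judged.

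**Conclusion.** The point holds in a limited form: a cheap improvement, not a design error. The one inferential method stated for safety cannot measure the risk of injection-specific complications, and at this sample size it has little power for harms of a few percent. The size depends on assumed rates: with 64 per arm, no loss and 0% in controls, Fisher misses 99%, 90% and 37% at true PRP rates of 3%, 5% and 10%. The 5.6% upper limit for 0 of 64 needs no assumption about the true rate, only that all 64 patients are treated and assessed. The PHN sample size is not in question.

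**What to change.** **Statistical Analysis, Secondary Outcomes.** Stop using the complication rate as the example for the chi-square or Fisher test. State instead that:

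- injection-related complications will be reported for the PRP arm, per patient treated, with an exact (Clopper-Pearson) 95% confidence interval;
- adverse events that can occur in both arms will be reported as a risk difference with a 95% confidence interval;
- a non-significant difference will not be taken as evidence of safety.

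**Strengths and Limitations.** Restrict the remark on adequate power to the PHN outcome, and add that 0 complications in 64 PRP patients would exclude only per-patient rates above about 5.6%.

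**Cost.** A few sentences and a few table columns, with no new data or patients. The price is a visibly weaker safety conclusion, which is what a trial of this size can support.

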#### Sample Size Calculation

Based on the reported prevalence, the incidence of PHN after antiviral therapy with famciclovir after VZV relapse in patients > 50 years of age is approximately 34.8%[31]. We predict a similar incidence rate in the control group. For the PRP group, our clinical experience suggests an estimated incidence of 10%. To achieve a 90% confidence level and a 5% significance level, we used PASS V.15 software (NCSS, Kaysville, UT, USA) to estimate that a minimum of 58 patients per group is required. Considering a potential 10% dropout rate, we plan to recruit 64 patients per group, totaling 128 patients.

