## Strengths and Limitations

Ultrasound-guided paravertebral PRP injections provide a minimally invasive approach for managing ZAP. By activating the body's natural healing, PRP may serve as an effective alternative to traditional antiviral and pain treatments, with fewer systemic side effects. This study could introduce a new option for alleviating ZAP and preventing PHN, enhancing patient quality of life and reducing reliance on medications.

However, certain limitations must be considered. Firstly, the quality of PRP preparation may vary due to technical aspects and operator proficiency, potentially affecting the consistency of therapeutic outcomes. Secondly, despite a sample size calculation ensuring adequate statistical power, the small sample size and geographical limitations of the study sites may restrict the generalizability of the results.

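### The sample-size paragraph labels its power as a 90% confidence level, and its dropout allowance leaves marginally fewer than the stated minimum of 58 per group

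*Protocol article*

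**What the plan says.** In the protocol article, Sample Size Calculation takes the control rate from a cited source: PHN incidence on famciclovir in patients over 50 "years of age is approximately 34.8" per cent. For the PRP arm, "our clinical experience suggests an estimated incidence of 10" per cent. The error rates are given as "To achieve a 90% confidence level and a 5% significance level", and PASS then returns a minimum of 58 per group. The allowance for losses follows: "Considering a potential 10% dropout rate, we plan to recruit 64 patients per group, totaling 128 patients". The paragraph does not use the word power.

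The neighbouring sections fix the other inputs. Under Statistical Analysis, Primary Outcome says "A chi-square test will be used to compare the incidence of PHN" and plans a 95% confidence interval for the relative risk. Secondary Outcomes says "All statistical analyses will use two-sided tests, with the significance level set to 0.05". Strengths and Limitations later speaks of the small sample "despite a sample size calculation ensuring adequate statistical power".

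Two descriptions of PHN appear. Background gives the conventional definition, "pain in the affected dermatome that persists for at least 3 months after the healing of the acute herpes zoster rash", with no intensity threshold. Outcome Assessment, Primary Outcome counts patients with an NRS score of 4 or more at 3, 6 and 12 months.

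**The concern.** Confidence level and significance level are complements. A two-sided 5% test pairs with a 95% interval, which is also the interval planned for the relative risk. A 90% confidence level beside a 5% significance level is therefore self-contradictory, and the power, which the paragraph needs, is missing. A reader who takes the wording literally could suppose that the trial was sized at a 10% level, or that its power is unknown. Strengths and Limitations nevertheless relies on this calculation for its assurance about power.

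The dropout step has a separate slip. If 58 is a minimum and 10% are lost, the number recruited should leave at least 58, and 64 does not quite do so.

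Finally, the paragraph does not say which PHN definition or time point the 34.8% refers to, while the trial's endpoint is narrower than the definition in Background.

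**Working it through.** **Inputs.** Control rate p1 = 0.348 and PRP rate p2 = 0.10 (Sample Size Calculation); two-sided α = 0.05 (Statistical Analysis, Secondary Outcomes); chi-square test (Statistical Analysis, Primary Outcome); 1:1 allocation (Randomization and Blinding).

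**Step 1: reproduce 58.** Pooled two-proportion formula, no continuity correction:

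n = [z(α/2)·√(2p̄q̄) + z(β)·√(p1q1 + p2q2)]² / (p1 − p2)²

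- p̄ = (0.348 + 0.10)/2 = 0.224 and q̄ = 0.776, so √(2 × 0.224 × 0.776) = 0.5896.
- p1q1 + p2q2 = 0.2269 + 0.0900 = 0.3169, with square root 0.5629.
- At 90% power: (1.960 × 0.5896 + 1.2816 × 0.5629)² / 0.248² = 3.523/0.0615 = 57.3, rounded up to **58**. This is the protocol's figure.

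**Step 2: try other readings of the 90%.**

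| Setting | n per group |
|---|---|
| Two-sided 5%, 90% power, pooled, uncorrected | 58 |
| Two-sided 5%, 90% power, continuity-corrected | 66 |
| Two-sided 5%, 90% power, unpooled variance | 55 (54.1) |
| Two-sided 5%, 90% power, arcsine | 55 |
| Two-sided 5%, 85% power, uncorrected / corrected | 50 / 57 |
| Two-sided 5%, 80% power, uncorrected / corrected | 44 / 51 |
| 90% confidence taken literally (two-sided 10%, same as one-sided 5%), 90% power, uncorrected / corrected | 47 / 55 |
| As above, 80% power, uncorrected / corrected | 34 / 42 |

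Only the first row gives 58.

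**Step 3: dropout.**

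- Correct inflation: 58/(1 − 0.10) = 64.4, i.e. 65 per group, 130 in total.
- What matches the plan: 58 × 1.10 = 63.8, i.e. 64 per group, 128 in total.
- Left after 10% dropout: 64 × 0.90 = 57.6.
- Dropout that 64 can absorb: 1 − 58/64 = 6/64 = 9.4%.

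**Step 4: what the shortfall costs.** Power = Φ{[(p1 − p2)√n − z(α/2)√(2p̄q̄)] / √(p1q1 + p2q2)}:

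| n per group | Power |
|---|---|
| 57 | 89.9% |
| 57.6 | 90.2% |
| 58 | 90.4% |
| 64 | 92.9% |

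The expected 57.6 is below the rounded minimum of 58 but above the unrounded 57.3, so expected power stays at about 90%.

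**Step 5: endpoint and control rate.** At any one visit, patients with NRS of 4 or more are a subset of those with any pain, so the endpoint is narrower than the definition in Background. The documents do not say which definition the cited 34.8% used, so no corrected n follows from them.

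**The case against.** The best defence is that nothing of substance turns on this. The number 58 is right, the intended meaning of the 90% can be recovered, and the analysis sections fix a two-sided 0.05 level and a 95% interval, so the slip changes no analysis. On dropout, 0.4 of a patient per group is negligible. The plan also includes an intention-to-treat analysis with multiple imputation and tries to complete a last follow-up for dropouts. The intention-to-treat set could therefore keep all 64 per group, with nominal power up to 92.9%, though imputation does not recover all the lost information. All of this stands, and it limits the point to a correction of wording. It does not make the sentence right: a figure the trial relies on carries the wrong name, and the stated dropout does not leave the stated minimum.

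A reader might go further and infer that the trial is underpowered, because 34.8% describes any persisting pain while the endpoint needs NRS of 4 or more. The documents do not support that. The source's definition is not shown, and Background does not say that 34.8% rests on the definition given there. The control rate could also move either way. The threshold could lower it. But entry requires age 50 or over and NRS of 4 or more, and Background links older age and severe initial pain to PHN despite antivirals, which could raise it. With control rates that are assumptions only, 58 per group and the same relative risk (0.10/0.348), power would be 84% at a control rate of 30% and 95% at 40%. With the PRP rate held at 10%, it would be 78% and 97%. Quoting only the downward cases would overstate the concern.

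**Conclusion.** Two statements are wrong as written, and both are minor in effect. First, the 90% is power, not confidence. This rests on exact reproduction of 58 from the protocol's own rates with the uncorrected chi-square test at two-sided 5%. Second, 64 per group allows 9.4% dropout and not 10%. At the assumed rates the gap is about half a percentage point of power (89.9% at 57 against 90.4% at 58), so it is no evidence of an underpowered trial and no reason to enlarge it.

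The basis of the 34.8% is a request for clarification, not an established error. What can be said is that the assurance about power in Strengths and Limitations is unconditional, whereas it holds only if 34.8% and 10% are the rates for the endpoint as defined.

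**What to change.** 1. In Sample Size Calculation, replace the confidence-level wording with a statement such as: *58 per group gives 90% power (two-sided 5%, chi-square) for 34.8% versus 10%; 64 per group allows 9.4% dropout.* The planned total of 128 stays.
2. In the same paragraph, state the PHN definition and time point behind the 34.8%, and say how they relate to the endpoint of NRS of 4 or more.
3. In Strengths and Limitations, claim adequate power only under the assumed rates.

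The cost is a few sentences. Design, recruitment target, outcomes and analysis do not change.
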